### Outcome measures

The primary endpoint of this study is the rate of binary restenosis (stenosis of at least 50% of the luminal diameter) or PSVR (peak systolic velocity ratio) ≥2.5 or 0 (PSVR = peak systolic velocity within the area of stenosis divided by peak systolic velocity in a normal adjacent proximal artery segment) in the treated segment at 12 months after the intervention as determined by catheter angiography or duplex ultrasound. The secondary endpoints are as follows: 1) composite of binary restenosis and major stent fracture (moderate or severe stent fracture); 2) stent fracture rate according to fracture grade (minor, moderate, severe); 3) limb salvage rate free of above-the-ankle amputation; 4) sustained clinical improvement rate at 12-month follow-up; 5) repeated target lesion revascularization (TLR) rate; 6) repeated target extremity revascularization (TER) rate; 7) total reocclusion rate; 8) comparison of angiograph variables consisting of late loss and restenosis rate; 9) ankle-brachial index (ABI) at 12 months; 10) the rate of major adverse cardiovascular events (MACE) composed of all-cause death, myocardial infarction, repeat percutaneous coronary intervention (PCI), and stroke at 12 months; 11) incidence of geographic miss during stent deployment due to jumping and/or elongation; 12) rate of binary restenosis or PSVR ≥2.5 or 0 according to clopidogrel and cilostazol; and 13) major bleeding rate between clopidogrel and cilostazol group. The detailed definitions are summarized in the Appendix.

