### Statistical analysis

#### Sample size calculation

From previous studies, including ABSOLUTE [7], FAST [8], and ASTRON [9], recurrence rates in femoropopliteal lesions after one year were 32%, 34.4%, and 37%, respectively - approximately 35% on average. The recurrence rate for the SMART™ CONTROL stent was 34.8% in the SUPER-SL study - a multicenter, randomized controlled trial that compared two self-expanding nitinol stents, the SMART™ CONTROL and Luminexx stents, in femoropopliteal lesions [14]. So far, there are limited data on the one-year primary patency rate of the COMPLETE™-SE stent. Based on previous research results, the SMART™ CONTROL stent group will be the control group, and the COMPLETE™-SE stent group will be the experimental group. Based on the SUPER-SL results, the one-year primary patency of the SMART™ CONTROL stent is estimated to be 65% and the one-year primary patency of the COMPLETE™-SE stent is estimated to be 80%, which is higher than that of the SMART™ CONTROL stent. Recurrence will be defined as more than 50% restenosis or total occlusion under invasive angiography, or if invasive angiography is not performed, PSVR ≥2.5 when evaluated with duplex ultrasound. The statistical significance level is set at 5%, the power of test is set as 80%, and the randomization ratio is set as 1:1. Test for proportion and chi-square method are used. Using standard sample size formula, it was calculated that 138 patients per group are needed for a total of 346 patients, after accounting for a 20% dropout rate.

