## Appendix

### Endpoints definitions

Binary restenosis: defined as a reduction in the luminal diameter of >50% according to the worst angiographic view at the narrowest site within the treated segment plus the 10-mm segments proximal and distal to the treated segment by catheter angiography or PSVR ≥2.5 (PSVR = peak systolic velocity within the area of stenosis divided by peak systolic velocity in a normal adjacent proximal artery segment) or total occlusion by duplex ultrasound. Stent fracture rate according fracture grade (minor, moderate, severe) [12]: plain X-ray examinations for the stent fracture are used or performed using at least two different angulations (30 to 45° difference) and the highest available magnification. Stent fracture is classified as minor (single strut fracture), moderate (fracture of more than 2 struts), or severe (complete separation of stent segments). Target lesion revascularization (TLR): defined as any repeat percutaneous intervention of the target lesion or bypass surgery of the target vessel performed for restenosis because of a return of ischemic symptoms, decrease of at least 1 Rutherford category, decrease in the ankle brachial index of >0.15, or restenosis of >50% as measured by catheter angiography. The target lesion is defined as the treated segment from 10 mm proximal to the stent and to 10 mm distal to the stent. Target extremity revascularization (TER): defined as any repeat percutaneous intervention of the target extremity or bypass surgery of the target extremity performed for restenosis because of a return of ischemic symptoms, decrease of at least 1 Rutherford category, decrease in the ankle brachial index of >0.15, or restenosis of >50% as measured by catheter angiography. Limb salvage: defined as survival free of amputation. Amputation is defined as above-ankle amputation of the index limb. Sustained clinical improvement rate [36, 37]: defined as persistent ABI value ≥0.15 and persistent improvement of ≥1 class according to Rutherford throughout follow-up when compared with baseline without the need for repeat TLR in surviving patients. Late loss: defined as a change in MLD from final angiogram to follow-up. Major adverse cardiac events (MACE): defined as composite of all-cause death, myocardial infarction, cerebrovascular stroke, and target lesion revascularization.

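### The primary endpoint has three differing wordings and no rule for restenosis treated before month 12, so a known failure can be scored patent or dropped

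*Protocol article*

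**What the plan says.** All places are in the Protocol article.

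- **Outcome measures** gives the primary endpoint as "binary restenosis (stenosis of at least 50% of the luminal diameter"), or a peak systolic velocity ratio (PSVR) of 2.5 or more, or of 0. It is read "in the treated segment at 12 months after the intervention as determined by catheter angiography or duplex ultrasound". TLR appears separately, as secondary endpoint 5. The section refers to the Appendix for detailed definitions.
- **Appendix, Endpoints definitions** has binary restenosis "defined as a reduction in the luminal diameter of >50% according to the worst angiographic view", in the treated segment "plus the 10-mm segments proximal and distal to the treated segment by catheter angiography", or PSVR of 2.5 or more, or total occlusion, on duplex. It states no time point.
- **Sample size calculation** defines recurrence as more than 50% restenosis or total occlusion on invasive angiography, or "if invasive angiography is not performed, PSVR ≥2.5 when evaluated with duplex ultrasound". It has no duplex occlusion term and no time point. The planning figures are one-year primary patency of 65% (SMART CONTROL) and 80% (COMPLETE-SE).
- **Randomization and interventions** recommends imaging once, at 12 months, by angiography or duplex according to local practice.
- **Statistical analysis** applies the chi-square or Fisher's exact test to the 12-month binary restenosis rate, excludes missing data for the major endpoints, and adds that cumulative restenosis rates will be calculated at the end of the 12 months.

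**The concern.** The same patient can be a success or a failure depending on which section the analyst follows, and nothing prevents that choice from being made after the data are seen.

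Timing is the more serious problem. Consider a patient whose stent restenoses, who has TLR at month 6, and whose vessel is open at month 12. Primary patency has been lost, but the status at 12 months is patent. If the same patient has no 12-month image, the missing-data rule removes the patient from the analysis. The Appendix defines TLR as reintervention performed for restenosis, so this is a known failure that the primary comparison need not count. The objectives and the sample size both rest on primary patency. The test may therefore be run on a different and smaller quantity than the one it was planned for.

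**Working it through.** **1. The three wordings side by side**

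| Element | Outcome measures | Sample size calculation | Appendix |
|---|---|---|---|
| Angiographic threshold | 50% or more | more than 50% | more than 50% |
| Segment | treated segment | not stated | treated segment plus 10-mm margins |
| Modality order | either, unranked | angiography first | either, unranked |
| Occlusion on duplex | counted (PSVR 0) | not mentioned | counted |
| Time point | at 12 months | none stated | none stated |

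The threshold difference matters only at exactly 50%. The segment difference changes the result for any edge restenosis. The modality difference matters whenever both images exist and disagree.

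**2. The plan's own sample size**

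Inputs from Sample size calculation: restenosis p₁ = 1 − 0.65 = 0.35 and p₂ = 1 − 0.80 = 0.20; "The statistical significance level is set at 5%, the power of test is set as 80%, and the randomization ratio is set as 1:1"; chi-square test; 20% dropout. Sidedness is not stated there; two-sided is used because it reproduces the figure.

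n = [1.960·√(2·p̄·q̄) + 0.8416·√(p₁q₁ + p₂q₂)]² / (p₁ − p₂)², with p̄ = 0.275 and q̄ = 0.725

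= [1.960·√0.39875 + 0.8416·√0.3875]² / 0.15² = (1.2377 + 0.5239)² / 0.0225 = 137.9, so **138 per group**.

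138 / 0.8 = 172.5, so 173 per group and **346 in total**. Both figures match the plan, and power at 138 per group is 80.0%.

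**3. Restenoses scored patent, equal share in both arms**

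Let f be the share of restenoses scored patent. The documents give no value, so f is an assumption, shown from 5% to 30%. The observed rates are 0.35(1 − f) and 0.20(1 − f).

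Power = Φ{[√n·(p₁ − p₂) − 1.960·√(2·p̄·q̄)] / √(p₁q₁ + p₂q₂)}, computed with the observed rates.

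| f | Observed rates | Power, 138 per group | n per group for 80% |
|---|---|---|---|
| 0 | 35.0% vs 20.0% | 80.0% | 138 |
| 5% | 33.25% vs 19.0% | 77.2% | 149 |
| 10% | 31.5% vs 18.0% | 74.1% | 160 |
| 20% | 28.0% vs 16.0% | 67.4% | 186 |
| 30% | 24.5% vs 14.0% | 60.0% | 221 |

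If all 173 per group were evaluable, power would be 88.1% at f = 0, 83.2% at 10% and 77.1% at 20%.

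**4. Restenoses dropped instead**

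If the share f is excluded as missing, the observed rate is p(1 − f)/(1 − pf). At f = 20% this gives 0.28/0.93 = 30.1% and 0.16/0.96 = 16.7%. The difference is 13.4 points, against 15 planned.

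**5. Unequal shares**

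If only control-arm restenoses are reopened, f = 10% gives 31.5% vs 20%. The difference is 11.5 points and power is 59.0%. If only the experimental arm is affected, f = 20% gives 35% vs 0.20 × 0.80 = 16%, and the difference widens to 19 points. The estimate can move either way.

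**The case against.** The strongest reply is that the plan resolves most of this itself. Outcome measures points to the Appendix, so the Appendix could be taken to govern and to supply the 10-mm margins. The angiography-first rule could be taken as filling a silence elsewhere. This is partly fair, and the threshold mismatch alone would be trivial. But the Appendix differs from the section that cites it on threshold and segment, and gives no order of modalities. Its own TLR definition describes the treated segment as running from 10 mm proximal to 10 mm distal to the stent, while its restenosis definition adds 10-mm margins to the treated segment. The pointer does not settle the question.

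A second reply is that no sentence says a reopened lesion counts as patent, that primary patency language appears throughout, and that cumulative restenosis rates are promised. It is true that the misclassification is permitted rather than prescribed. However, the cumulative rates have no definition, no test and no stated link to the primary comparison, whereas the chi-square test is tied explicitly to the 12-month rate. How TLR is scored might be left to a full analysis plan. The point here is that the rules actually printed (12-month status, TLR as secondary, missing data excluded) together point away from primary patency.

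Three stronger readings are tempting and are not supported:

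- *Occlusions on duplex are scored patent.* Only the recurrence sentence in Sample size calculation omits them. Outcome measures and the Appendix both count them, and Statistical analysis defines recurrence to include total occlusion.
- *Every wording is tied to status at 12 months.* Only Outcome measures and the label used in Statistical analysis fix that time.
- *The stated power is lost.* The sample size reproduces exactly. Any loss depends on a share that the documents do not give, and it comes from the timing gap, not from the differences in wording.

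**Conclusion.** The point holds in this form: the primary endpoint is worded inconsistently in three places, and the stated rules allow a restenosis treated before month 12 to be scored patent or excluded, while the planning rates are one minus one-year primary patency. The sample size arithmetic is sound. The effect on power is conditional. It is about 3 points lost if 5% of restenoses are scored patent, 6 points at 10%, 13 at 20% and 20 at 30%, assuming equal shares in both arms and 138 evaluable patients per group. With fewer dropouts than planned, part of that loss would be absorbed. Unequal early TLR is the greater threat to interpretation, because it biases the difference itself. With recruitment ongoing, this can still be settled.

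**What to change.** 1. Use one definition, word for word, in Outcome measures, Sample size calculation and the Appendix. It needs one threshold, one analysis segment that includes the 10-mm margins (stating what they are measured from), angiography taking priority when both modalities are available, and occlusion on either modality counted as restenosis.
2. State that TLR for restenosis, or documented restenosis or occlusion, at any time up to the 12-month visit is a primary event, whether or not a 12-month image exists. The missing-data exclusion then no longer removes known failures.
3. Keep the 12-month imaging-only rate as a sensitivity analysis, and say whether the cumulative restenosis rate is the primary quantity or a description.

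With this change the 35% and 20% planning rates match the endpoint, so 138 per group and 346 in total stand without recalculation. The cost is a wording amendment and an edit check on the case report form. The downside is that the primary result is no longer a pure 12-month imaging estimate; the sensitivity analysis preserves that figure.

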### Statistical analysis

#### Sample size calculation

From previous studies, including ABSOLUTE [7], FAST [8], and ASTRON [9], recurrence rates in femoropopliteal lesions after one year were 32%, 34.4%, and 37%, respectively - approximately 35% on average. The recurrence rate for the SMART™ CONTROL stent was 34.8% in the SUPER-SL study - a multicenter, randomized controlled trial that compared two self-expanding nitinol stents, the SMART™ CONTROL and Luminexx stents, in femoropopliteal lesions [14]. So far, there are limited data on the one-year primary patency rate of the COMPLETE™-SE stent. Based on previous research results, the SMART™ CONTROL stent group will be the control group, and the COMPLETE™-SE stent group will be the experimental group. Based on the SUPER-SL results, the one-year primary patency of the SMART™ CONTROL stent is estimated to be 65% and the one-year primary patency of the COMPLETE™-SE stent is estimated to be 80%, which is higher than that of the SMART™ CONTROL stent. Recurrence will be defined as more than 50% restenosis or total occlusion under invasive angiography, or if invasive angiography is not performed, PSVR ≥2.5 when evaluated with duplex ultrasound. The statistical significance level is set at 5%, the power of test is set as 80%, and the randomization ratio is set as 1:1. Test for proportion and chi-square method are used. Using standard sample size formula, it was calculated that 138 patients per group are needed for a total of 346 patients, after accounting for a 20% dropout rate.

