**Methods/Design:**

The primary purpose of our study is to examine the incidence of stent fracture and primary patency between two different major representative self-expanding nitinol stents (SMART™ CONTROL versus COMPLETE™-SE) in stenotic or occlusive femoropopliteal arterial lesion. The secondary purpose is to examine whether there is any difference in efficacy and safety between aspirin plus clopidogrel versus aspirin plus cilostazol for one month following stent implantation in femoropopliteal lesions. This is a prospective, randomized, multicenter trial to assess the efficacy of the COMPLETE™-SE versus SMART™ CONTROL stent for provisional stenting after balloon angioplasty in femoropopliteal arterial lesions. The study design is a 2x2 randomization design and a total of 346 patients will be enrolled. The primary endpoint of this study is the rate of binary restenosis in the treated segment at 12 months after intervention as determined by catheter angiography or duplex ultrasound.

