All ipsilateral iliac arterial lesions should be treated with angioplasty and/or stenting concomitantly and residual stenosis should be less than 50%. Treatment of tibioperoneal lesions is recommended only in cases of critical limb ischemia. There should exist at least one patent (<50% stenosis) tibioperoneal run-off vessel with good antegrade flow.

A final angiography will be performed after the intervention in both groups, with the use of the same angles and magnifications used in the baseline angiograms. Simultaneously, reference vessel diameter (RVD), minimal luminal diameter (MLD), percent diameter stenosis, and acute gain should be measured. The reference vessel diameter will be obtained from averaging 5-mm segments proximal and distal to the lesion. Technical success will be defined as the successful access and deployment of the stent and less than 30% diameter residual stenosis after the revascularization.

For the post-procedural medication, aspirin 100 mg and clopidogrel 75 mg will be administered once daily for one month. Then, patients of each group will be randomized by web-based randomization to receive either clopidogrel 75 mg or cilostazol 100 mg once daily in addition to aspirin 100 mg for at least 11 months in a 1:1 manner.

After enrollment and index procedure, clinical follow-up will be planned at 1, 6, and 12 months to evaluate clinical outcomes and ankle-brachial index score. Also, all patients will be recommended to have a follow-up catheter angiography or duplex ultrasound at 12 months according to local clinical practice. The incidence of stent fracture and binary patency will be assessed by plain X-ray and quantitative femoral angiography. The investigators will be urged to follow up on patients, either by office visits or by telephone contacts, as necessary. Patient adherence to the study drug and side effects will be checked and monitored at every outpatient visit. The decision of drug discontinuation will be discussed and checked under the physician’s recommendation.

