### Statistical analysis

Categorical variables will be expressed as delivery rate when comparing baseline features between the SMART™ CONTROL and COMPLETE™-SE stent groups or the clopidogrel and cilostazol groups, and for categorical variables, comparisons between groups will use the chi-square or Fisher’s exact test. Continuous variables will be expressed as mean ± standard deviation, and for continuous variables, comparisons between groups will use the Student’s t-test. The primary and secondary endpoints will be analyzed using both intention-to-treat analysis (all subjects assigned to a treatment group) and per-protocol analysis (only subjects completed the treatment protocol). Study endpoints will also be analyzed per patient. For the primary endpoint (12-month binary restenosis rate) comparisons of the two patient groups will use the chi-square or Fisher’s exact test. At the end of the 12 months, cumulative restenosis rates will be calculated. All secondary endpoint analysis will be performed using the Student’s t-test, chi-square test, or Fisher’s exact test. Also, clinical outcomes such as revascularization of the target vessel, death, major cardiovascular events including myocardial infarction and cerebral infarction, and limb salvage rates will be analyzed using Kaplan-Meier survival estimates and a comparison of the groups will be performed using the log-rank test. A *P* value <0.05 is considered to be statistically significant. In order to evaluate the risk factors for recurrence, defined as restenosis or total occlusion, univariate and multivariate logistic regression analysis will be performed. Present research has concluded that there will be a very low chance of missing data to cause bias, and therefore, missing data for the major endpoints will be excluded from the analysis data. For repeated measurements for the secondary endpoints, last observation carried forward (LOCF) can be applied. The SPSS 20.0 (SPSS Inc, Chicago, Illinois, United States) statistics program will be used for all analysis.

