### Rationale of randomized trials comparing clopidogrel and cilostazol following femoropopliteal stenting

To date, in many previous reports, dual antiplatelet therapy consisting of aspirin and clopidogrel has proven to decrease the incidence of cardiovascular death, myocardial infarction, and revascularization without an increase in major bleeding in patients who have undergone PCI regardless of stent type (bare metal stent or drug-eluting stent) [25–27]. In 2011 the ESC guidelines recommended dual antiplatelet therapy with aspirin and a thienopyridine such as clopidogrel for at least one month after infra-inguinal bare metal stent implantation (Class I, Level C). However, there has been no definite evidence or guideline for the optimal antiplatelet agent after stent implantation beyond one month later [17]. There have been many studies for the efficacy of thienopyridines in peripheral arterial disease. In the Swedish Ticlopidine Multicenter Study (STIMS) 687 patient of intermittent claudication were treated with ticlopidine or placebo, and the incidence of fatal or non-fatal myocardial infarction and stroke was reduced in the ticlopidine group [28]. A randomized blinded trial of clopidogrel versus aspirin in patients at risk of ischemic events (CAPRIE) demonstrated that clopidogrel was better in treating peripheral artery disease than aspirin (relative risk reduction in composite end point: 23.8%) [29]. Based on this trial, clopidogrel has been approved for prevention of ischemic events in patients with peripheral artery disease by the United State Food and Drug Administration [29]. Clopidogrel is effective in reducing cardiovascular events in a subgroup of patients with symptomatic peripheral arterial disease, with or without other clinical evidence of cardiovascular disease [11]. In the CHARISMA (Clopidogrel for High Atherothrombotic Risk and Ischemic Stabilization, Management, and Avoidance) trial, the large number of patients with documented prior myocardial infarction, ischemic stroke, or symptomatic peripheral artery disease appeared to derive significant benefit from dual antiplatelet therapy with clopidogrel plus aspirin beyond aspirin alone [30]. In the CASPAR (Results of the randomized, placebo-controlled clopidogrel and acetylsalicylic acid in bypass surgery for peripheral arterial disease) trial, the combination of clopidogrel plus aspirin did not improve limb or systemic outcomes in the overall population of peripheral artery disease patients requiring below-knee bypass grafting [31]. Subgroup analysis suggests that clopidogrel plus aspirin confers benefit in patients receiving prosthetic grafts (Hazard ratio: 0.65; 95% CI: 0.45-0.95; *P* = 0.025) without significantly increasing risk of major bleeding [31]. With the potential benefit of cilostazol on vascular function *in vitro*, there have been several previous efforts to prove the efficacy of cilostazol in patients undergoing endovascular therapy or stent implantation in peripheral arterial disease. For example, Soga *et al*. and Iida *et al.* have reported that cilostazol may improve amputation-free survival and limb salvage rate after endovascular therapy for infrainguinal disease in patients with critical limb ischemia and intermittent claudication [19, 32–34]. Also, they have demonstrated that cilostazol reduced restenosis after superficial femoral artery stenting with a self-expandable nitinol stent and it seems to be more effective in patients who are at a high risk of restenosis [35]. However, very few trials have not effectively or properly addressed the direct comparison for the efficacy and safety between clopidogrel and cilostazol. This trial is designed to evaluate the efficacy and safety between aspirin plus clopidogrel versus aspirin plus cilostazol in patients undergoing stent implantation in femoropopliteal lesions.

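### Stent and antiplatelet drug are both randomized and both judged on restenosis, but the primary test ignores the drug factor and the stent sample size does not say what drug background its 35% control rate assumes

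*Protocol article*

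**What the plan says.** The abstract (Methods/Design) declares a two-factor trial: "The study design is a 2x2 randomization design and a total of 346 patients will be enrolled". Under Randomization and interventions, everyone starts on aspirin plus clopidogrel during the first month. After that comes the second allocation: "patients of each group will be randomized by web-based randomization to receive either clopidogrel 75 mg or cilostazol 100 mg once daily", on top of aspirin, in a 1:1 ratio for at least 11 months.

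The primary endpoint is 12-month binary restenosis by stent. Secondary endpoint 12 (Outcome measures) is the same restenosis measure by drug.

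The Sample size calculation deals with the stent factor only. Its control rate is historical: "The recurrence rate for the SMART™ CONTROL stent was 34.8% in the SUPER-SL study", close to the roughly 35% average of three other trials. Hence "Based on the SUPER-SL results, the one-year primary patency of the SMART™ CONTROL stent is estimated to be 65" per cent, and "the one-year primary patency of the COMPLETE™-SE stent is estimated to be 80" per cent. Further, "The statistical significance level is set at 5%, the power of test is set as 80%, and the randomization ratio is set as 1:1". The result is 138 per group, or 346 in total with 20% dropout. The antiplatelet randomization is not mentioned there.

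Under Statistical analysis: "For the primary endpoint (12-month binary restenosis rate) comparisons of the two patient groups will use the chi-square or Fisher’s exact test". Secondary endpoints, and so endpoint 12, get a t-test, chi-square or Fisher's exact test. Neither comparison takes account of the other randomized factor.

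The rationale section on clopidogrel and cilostazol cites work reporting that "cilostazol reduced restenosis after superficial femoral artery stenting with a self-expandable nitinol stent".

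**The concern.** The second factor was added partly because cilostazol may lower restenosis, which is the outcome on which the first factor is sized and tested. Half of each stent arm is assigned cilostazol for most of the time to the primary endpoint. The control arm as run is therefore SMART CONTROL on a 50:50 clopidogrel/cilostazol background, while 35% comes from earlier trials whose antiplatelet background the article does not describe. If that background matters, the control rate in this trial may not be 35%, and the power at 138 per arm changes with it.

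The analysis has a matching gap. In a 2x2 trial with both factors acting on one outcome, the natural comparison of each factor is made within levels of the other. The article fixes a crude test for each, so the analysis does not follow the declared design and does not show whether the stent effect is similar on the two drugs.

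At stake is how the primary result is read. A null stent result would be taken as coming from an 80%-powered trial, with no statement of the drug background on which that figure rests.

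**Working it through.** **Inputs from the article:** restenosis 35% (SMART CONTROL) and 20% (COMPLETE-SE); significance level 5%; power 80%; 1:1 allocation; 20% dropout; 1:1 drug assignment within each stent group. Sidedness is not stated; two-sided reproduces the plan.

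**Input assumed:** r, the relative reduction in restenosis from cilostazol against whatever background lies behind the 35%, equal in both stent arms. The documents give no value. I use 10%, 20% and 30%.

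**1. Reproduce the plan.** With p̄ = (p1 + p2)/2,

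n = [1.96·√(2p̄(1−p̄)) + 0.842·√(p1(1−p1) + p2(1−p2))]² / (p1−p2)²

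For 0.35 and 0.20, p̄ = 0.275. The two roots are 0.6315 and 0.6225, so n = (1.2377 + 0.5239)²/0.0225 = 137.9, giving 138. Then 138/0.80 = 172.5, rounded up to 173, and 2 × 173 = 346. Both figures match.

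**2. Power at 138 per arm.**

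Power = Φ{[(p1−p2)·√138 − 1.96·√(2p̄(1−p̄))] / √(p1(1−p1) + p2(1−p2))}

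At 35% versus 20%: (0.15 × 11.747 − 1.2377)/0.6225 = 0.842, and Φ(0.842) = 80.0%.

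**3. Put half of each arm on cilostazol.** The pooled control rate is 0.35·(1 − r/2). The experimental rate depends on the scale on which the stent effect is held:

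- constant relative risk, 0.20/0.35 = 0.571: 0.20·(1 − r/2)
- constant odds ratio, (0.20/0.80)/(0.35/0.65) = 0.464, applied within each drug group and then averaged
- constant difference: control rate minus 0.15

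| Assumed r | Control rate | Experimental rate at constant RR | Power, constant RR | Power, constant OR | Power, 15-point difference kept |
|---|---|---|---|---|---|
| 0 | 35.0% | 20.0% | 80.0% | 80.0% | 80.0% |
| 10% | 33.25% | 19.0% | 77.2% | 78.4% | 81.7% |
| 20% | 31.5% | 18.0% | 74.1% | 76.5% | 83.5% |
| 30% | 29.75% | 17.0% | 70.8% | 74.2% | 85.4% |

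The direction of the change depends on the scale.

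**4. Crude versus stratified test.** The Mantel-Haenszel statistic sums observed minus expected restenoses over the strata of the other factor and divides its square by the summed hypergeometric variances. In simulation with 69 patients per cell and constant relative risks, power for the stent comparison went from 71.3% (crude) to 71.7% (stratified) at r = 30%, and from 64.2% to 65.6% at an extreme r = 50%. For the drug comparison with no drug effect but the planned stent effect, the type I error was 4.65% crude and 4.97% stratified, so the crude test is mildly conservative.

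**The case against.** A reader might infer that the 80% holds only if cilostazol does nothing, or that on its own rationale the trial has about 64% to 74% power. The documents do not support either reading.

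- **Scale.** The article assumes two absolute rates and never states a relative risk. At those rates 80% is correct, and if the 15-point difference is kept, power rises.
- **Direction of the secondary aim.** It asks whether the regimens differ. The Background calls the cilostazol restenosis evidence small-scale or retrospective and says that no randomized comparison with clopidogrel exists.
- **Size and background.** No effect size is given, nor the antiplatelet treatment behind the 35%. The 64% needs a 50% reduction, for which the documents offer no basis.
- **Other uncertainties.** The control rate could also be above 35%, since the criteria include critical limb ischemia and set no lesion-length limit. With an assumed 40% base rate and the same relative risk, power is 81.6% at r = 20% and 78.4% at r = 30%. If all 173 per arm were evaluable, power at r = 30% and constant relative risk would be 80.3%.
- **Exposure.** The abstract describes the drug comparison as lasting one month, whereas Randomization and interventions has it begin after one month and run for at least 11. These passages must be reconciled before any exposure is assumed.
- **Validity of the crude test.** Drug is assigned 1:1 within each stent group, so the unadjusted stent comparison is valid as a marginal one.

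All of this stands against a claim of underpowering. One reply also stands. If the clopidogrel group has 35% versus 20%, keeping 15 points on cilostazol at r = 20% means 28% versus 13%. That is a 35% cut with COMPLETE-SE against 20% with SMART CONTROL. The favourable case thus needs an interaction on the relative scale, which the article does not propose. It does not propose a constant relative risk either, so the assumption needs to be stated.

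**Conclusion.** The sample size is not wrong: 138 per group and 346 in total follow from 35% versus 20%. What holds is narrower. The sizing does not say what drug background its rates represent, and the tests fixed for both factors ignore the other randomized factor although both are judged on restenosis.

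For assumed cilostazol reductions of 10% to 30%, power at 138 per arm is about 77% to 71% at a constant stent relative risk and about 82% to 85% if the 15-point difference is kept. These figures rest on an equal relative drug effect in both stent arms and on cilostazol being better than the unknown background behind the 35%. They show sensitivity and do not estimate this trial's power.

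Stratifying adds little power (about 0 to 1.4 points). Its main merit is that the analysis then follows the 2x2 design and shows the stent effect on each drug.

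**What to change.** **Statistical analysis section.** Analyse restenosis with a Mantel-Haenszel test and risk difference: stents stratified by assigned drug, and drugs (endpoint 12) stratified by stent. Show the stent effect within each drug group.

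Keep the unadjusted intention-to-treat stent comparison of all stent-randomized patients alongside. Drug is randomized a month after the stent, so patients who never reach that step are defined by what happened after stent assignment, which the stent may have influenced. They should not form a stratum of the primary test; the unadjusted comparison retains them without that conditioning. Name in advance which of the two stent analyses carries the primary conclusion.

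**Sample size section.** State that 35% and 20% are taken as averages over the 50:50 drug background, and that power changes if that background shifts the control rate. The table above can serve as the sensitivity range, with both scales shown.

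**Cost.** Wording in two sections and a little extra analysis. Keep 346 patients; no procedures change. The only downside is a more cautious power statement.
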